# Protocol of a mixed method, randomized controlled study to assess the efficacy of a psychosocial intervention to reduce fatigue in patients with End-Stage Renal Disease (ESRD)

**DOI:** 10.1186/s12882-016-0277-8

**Published:** 2016-07-08

**Keywords:** Study protocol, End-stage renal disease, Fatigue, Quality of life, Psychosocial, Intervention, Social workers, Randomised controlled trial, Mixed methods, Process evaluation

## Abstract

**Background:**

Patients with end-stage renal disease (ESRD) commonly suffer from severe fatigue, which strongly impacts their quality of life (QoL). Although fatigue is often attributed to disease- and treatment characteristics, research also shows that behavioural, psychological and social factors affect perceived fatigue in dialysis patients. Whereas studies on fatigue in other chronic patient groups suggest that psychological or psychosocial interventions are effective in reducing fatigue, such interventions are not yet available for ESRD patients on dialysis treatment. The objective of this study is to examine the efficacy of a psychosocial intervention for dialysis patients aimed at reducing fatigue (primary outcome) and improving QoL (secondary outcome). The intervention consists of counselling sessions led by a social worker. The implementation process and patients’ and social workers’ expectations and experiences with the intervention will also be evaluated.

**Methods/Design:**

This study follows a mixed-methods design in which both quantitative and qualitative data will be collected. A multi-centre, randomised controlled trial (RCT) with repeated measures will be conducted to quantitatively assess the efficacy of the psychosocial intervention in reducing fatigue and improving QoL in ESRD patients. Additional secondary outcomes and medical parameters will be assessed. Outcomes will be compared to patients receiving usual care. A sample of 74 severely fatigued dialysis patients will be recruited from 10 dialysis centres. Patients will be randomly assigned to the intervention or control group. Outcomes will be assessed at baseline, post intervention/16 weeks, and at three and six-month follow-ups. A qualitative process evaluation will be conducted parallel to/following the effectiveness RCT. Interviews and focus groups will be conducted to gain insight into patients’ and social workers’ perspectives on outcomes and implementation procedures. Implementation fidelity will be assessed by audio-taped and written registrations. Participatory methods ensure the continuous input of experiential knowledge, improving the quality of study procedures and the applicability of outcomes.

**Discussion:**

This is the first mixed method study (including an RCT and qualitative process evaluation) to examine the effect and implementation process of a psychosocial intervention on reducing fatigue and improving QoL in ESRD patients on dialysis treatment.

**Trial registration:**

NTR5366, The Netherlands National Trial Register (NTR), registered August 26, 2015.

**Electronic supplementary material:**

The online version of this article (doi:10.1186/s12882-016-0277-8) contains supplementary material, which is available to authorized users.

## Background

End-stage renal disease (ESRD) is a common chronic illness with an increasing incidence and prevalence [1, 2]. In the Netherlands, over 16,000 patients require renal replacement therapy due to severe kidney failure [3]. Although renal transplantation is the most preferred treatment [4, 5], many patients cannot profit from this option because of the donor shortage [5, 6] or medical ineligibility for receiving a donor kidney [7, 8]. Consequently, many ESRD patients depend on dialysis treatment. In the Netherlands, around 6,500 ESRD patients receive either haemodialysis or peritoneal dialysis treatment [9]. Although dialysis treatment is life-saving, the burdens of treatment are substantial and the therapy only replaces 10–15 % of normal renal function [10]. Dialysis patients experience multiple enduring health problems, of which fatigue is one of the most frequent complaints [11–14]. The prevalence of (severe) fatigue in dialysis patients ranges from 60–97 % [15, 16]. Fatigue is known as a subjective, unpleasant symptom that can vary from tiredness to exhaustion, which interferes with individuals’ ability to function in their normal (physical and mental) capacity [17–19]. Fatigue limits patients’ daily activities and independence, is often perceived as a source of stress and is commonly associated with reduced quality of life (QoL) [12, 13, 17]. Fatigue in patients on dialysis is often attributed to disease and treatment characteristics like anaemia, inflammation, medication, dialysis intensity and frequency. Except for Erythropoietin (EPO) injections to prevent anaemia, no medication is known to affect/reduce feelings of fatigue [20–22]. Although fatigue is often perceived as a physiological side-effect of the chronic illness [12], research shows that fatigue is not only grounded in physiological factors. Fatigue seems to be caused by a complex interaction of biological processes, psychosocial phenomena and behavioural manifestations [19]. Previous research identified various behavioural, psychological and social factors influencing fatigue in long-term dialysis patients such as anxiety, stress, depression, sleep disorders, substance use, physical inactivity and (lack of) social support [12]. Another study also highlighted the complex character of fatigue in ESRD patients [17]. The authors made a distinction between physical, cognitive and affective fatigue, and identified various physiological, sociodemographic, psychological, behavioural and dialysis-related factors to affect those various dimensions of fatigue.

Non-pharmalogical interventions targeted at behavioural, psychological, cognitive and social factors, may potentially be successful in decreasing fatigue in dialysis patients. Studies on fatigue in patients with cancer [23–28], chronic pain [29], chronic fatigue syndrome [30, 31], brain injury [32] and muscular diseases [33, 34], suggest that such psychological or psychosocial interventions are effective in reducing fatigue that is caused by multiple interacting factors. As far as we know, the literature does not describe (evidence-based) psychological or psychosocial interventions to reduce fatigue in ESRD patients. This can be seen as a deficiency, since such interventions may, based on other populations and causes of fatigue, also be effective in reducing the experienced fatigue of patients on dialysis.

The primary objective of this study is to investigate the efficacy of a psychosocial intervention on the reduction of fatigue provided to patients on dialysis treatment, compared to dialysis patients receiving usual care. Secondary objectives are to study the efficacy of the intervention on improving the QoL and to investigate the possible mediating and moderating effects of coping style, illness cognitions and perceptions, catastrophizing thoughts, feelings of depression, feelings of control and mastery, and social support. A randomised controlled trial (RCT) will be conducted to achieve these objectives. Next to the RCT, a process evaluation will be conducted to gain an in-depth understanding of both patients’ and professionals’ expectations of, and experiences with the psychosocial intervention and its implementation. In addition, the degree to which the intervention is implemented as intended (implementation fidelity) will be evaluated [35–37].

## Methods/Design

### Design and setting

This study follows a mixed method design in which both quantitative and qualitative methods will be applied for data collection. The study involves a two-arm, multi-centre RCT involving patients with ESRD undergoing a dialysis treatment (either haemodialysis or peritoneal dialysis). Patients will be randomly assigned to either the intervention group (usual treatment and psychosocial counselling by a social worker in the dialysis department, aimed at reducing fatigue) or the control group (usual treatment). Intervention efficacy will be quantitatively measured (repeated measures/self-report questionnaires/medical records) (Fig. 1). A qualitative process evaluation will be conducted to gain insight into patients’ and professionals’ perspectives on outcomes and implementation procedures. Both interviews and focus groups will be applied for data collection. The study will be conducted at both academic and non-academic dialysis centres in the Netherlands. The aim is to include a maximum of 10 centres in total.

**Fig. 1 Fig1:**
[figure not shown]
Study design

### Research team and advisory group

#### Research team

The study will be conducted by a team of three researchers of the VU University Medical Centre (VUmc) and two patient research partners who are experiential experts in the field of kidney diseases/dialysis [38]. One them is a female patient (aged 48) suffering from kidney disease, the second one is a father (aged 66) of a patient who has been on dialysis treatment before transplantation. Both patient research partners are equal members of the research team and will participate in research activities throughout all study phases (research set-up, data collection and data analysis).

The surplus value of involving patient research partners in scientific research has been increasingly acknowledged. The experiential knowledge of patients complements the scientific perspective of academic researchers and contributes to the quality of research in various ways. It helps to assure that research is grounded in relevant clinical needs and targeted to patient-relevant outcomes, it can enhance study design and practicability, it improves data interpretation and it strengthens dissemination [39–42].

#### Advisory group

An advisory group consisting of patients, partners of renal patients and professionals will monitor the study and will be asked for input and feedback throughout all study phases. Participants are five patients/relatives (members of the Kidney Patients Association Netherlands - NVN), two social workers and a nephrologist. The advisory group will contribute to the quality of the study and applicability of outcomes by providing input from both patient and professional perspectives.

### Patient recruitment

In collaboration with the research team, the Dutch Association for Social Workers in Nephrology has informed its members about the opportunity to participate in this multi-centre study. Dialysis centres sign in to participate on a voluntary base. The local recruitment of patients within the participating centres will begin after formal approval is obtained by the head of the department, the local ethics committee and/or the board of directors. The social workers of the participating centres will be involved in the pre-screening and recruitment of patients at their centre (see inclusion and exclusion criteria below). They will be asked to identify all potential participants that fit the trial criteria within their patient population and to (randomly) invite suitable patients to participate in the study. The VUmc research team will provide a flyer and patient information letter to all participating centres in order to assure provision of identical study information to patients. The flyers and letters will be handed to the patients by the local social workers.

If a patient wants to participate, (after verbal consent) contact details will be sent to the first research executive [name], who will inform patients about the study procedures, answer questions and do a final check on inclusion and exclusion criteria. Subsequently, the first researcher will request that the patients fill out and return the Checklist Individual Strength (CIS-fatigue) questionnaire [43] in order to assess the perceived level of fatigue. If the score is ≥ 35, the final inclusion criterion is met. Patients will be informed about the survey results personally by phone, since we know from a former study that patients do not appreciate written communication about inclusion and exclusion [34]. After obtaining written informed consent and completion of the baseline measurement, participants will be randomly assigned to either the control or intervention group.

#### Sample size

The sample size calculation will be based on examining the difference between the psychosocial intervention versus usual care on the primary outcome ‘subjective experience of fatigue’ (four repeated measurements) [43]. Thirty-seven patients will be needed in each condition, assuming a significance of 5 % (two-tailed) and power of 80 % in detecting a clinically relevant change of eight points on the primary outcome variable [25, 44]. We expect a drop-out rate of 30 % based on an unpublished study by Dialysis Centre Groningen in 2011 (14 % mortality, 5 % kidney transplantation, 11 % remaining).

### Inclusion criteria

Adult patients (age ≥ 18), male or female, who undergo day dialysis (haemodialysis (HD), Peritoneal Dialysis (PD), at home, a hospital or a dialysis centre);Experiencing (severe) fatigue (score CIS-fatigue scale ≥ 35);Being able to walk/move for at least 10 min with or without a supporting device such as a walking stick;Having a sufficient understanding of the Dutch language in order to participate in counselling, (group) interviews and fill out the questionnaires adequately.

### Exclusion criteria

Dialysis during the night (since it is assumed that patients on day dialysis experience more severe fatigue compared to patients on night dialysis);Participation in other studies or treatments aimed at reducing fatigue;Treatment by a psychologist or psychiatrist (for severe psychiatric problems such as depression, psychosis, personality disorders or schizophrenia);Alcohol or drug addiction.

Furthermore, social workers will be asked to take into account the dialysis vintage (minimum of three months) and dialysis stability when pre-screening patients for the study.

### Randomisation

Patients who meet the trial criteria and give informed consent to participate in the study will be assigned to either the intervention or the control group. Patients in the control group will receive usual treatment. Patients in the intervention group will receive a protocolled psychosocial intervention provided by a social worker. Computer-generated block randomisation will be performed, ensuring the equal (1:1) allocation of patients to either the intervention or control group at each participating centre. To ensure concealment, the block sizes will not be disclosed. The allocation procedure is performed by an independent research colleague who is not involved in the study. The researcher [name] will inform patients about the allocation outcome and subsequent study procedures. For ethical reasons, and if desired, patients allocated to the control group will be offered the opportunity to participate in the intervention group after the third measurement. Due to the nature of the intervention neither participants nor social workers can be blinded to allocation. Data entry will be performed by a research assistant who is not informed about group allocation.

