### Data analysis

Descriptive statistics for outcome measures will be presented. A paired *t*-test will be used to investigate statistical significant differences in the effects (primary and secondary outcomes) between intervention and control groups. Statistical significance will be defined as *p* ≤ 0.05. Statistical analyses will be performed using the SPSS system for Windows, version 22.0. A detailed analysis plan will be developed in collaboration with a statistical expert. This plan will also address the analysis of potential effect modifiers and confounders, and further exploratory analyses.

Qualitative data will be subjected to a thematic analysis [55, 56]. Themes recurring from the data (interview and focus group transcripts) will be categorised and coded. The research team will meet on a regular basis and discuss emerging themes throughout the research process. Preliminary findings will be discussed with the members of the advisory group.

The quantitative outcomes will be related to, and integrated with the qualitative findings to determine correspondence and discrepancies in perceived and measured effects. The advisory group will be actively involved in discussing findings and final conclusions.

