## Discussion

As far as we know, this study will be the first (mixed method) study (including an RCT and qualitative process evaluation) to consider the effect of a psychosocial intervention on reducing fatigue and improving QoL in patients with ESRD on dialysis.

This study will have several strengths. First, the mixed method design of this study will allow for the integration of quantitative and qualitative findings, enhancing our understanding of intervention effects and implementation processes. Second, involving an advisory group and patient research partners will contribute to the overall quality of research and practical applicability of outcomes.

Existing psychological or psychosocial interventions to reduce fatigue in other patient groups often comprise cognitive behavioural therapy (CBT) provided by health psychologists/therapists [33, 44]. However, a randomised trial study [57] showed that counselling and CBT were equivalent in effect for patients with chronic fatigue in primary care. The psychosocial intervention in this study will be provided by social workers employed at the patient’s dialysis department. Besides cost efficiency, involving social workers will be the best option for various reasons. Whereas a care relationship between patients and social workers often already exists, and social workers are familiar with patients’ background and illness history, we expect this to be of added value in customising the intervention to each patient individually. We also expect that, for patients, the threshold to participate in counselling sessions with a social worker will be lower than the participation in psychological therapy with a psychologist they are not familiar with.

A potential limitation is that, by involving a various group of social workers to implement the intervention, treatment bias may occur. This will partly be countered by allocating an equal number of participants in both intervention and control groups at each participating centre. Furthermore, potential confounding effects will be explored by the assessment of implementation fidelity and exploring contextual dynamics by interviews with both patients and social workers.

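### The named between-group t-test leaves out centre, by which the trial blocks its randomisation, and equal allocation per centre does not deal with variation in how social workers deliver the counselling

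*Protocol article*

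**What the plan says.** The Randomisation section fixes the design: "Computer-generated block randomisation will be performed, ensuring the equal (1:1) allocation of patients to either the intervention or control group at each participating centre". Design and setting caps the number of centres at ten.

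Under Study intervention, a social worker already employed at the centre gives the counselling, and only to the intervention arm. The Implementation fidelity section asks each social worker to record a session with the second or third patient they counsel, so several patients per social worker are expected. No total number of social workers is given. The Interviews and focus groups section plans to invite eight to ten of them to a focus group.

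For the comparison of the arms, Data analysis says "A paired *t*-test will be used" and names no term for centre or social worker. It announces a detailed plan, to be written with a statistical expert, that will also cover effect modifiers, confounders and exploratory analyses.

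The Discussion recognises that using various social workers may bias the treatment comparison and adds: "This will partly be countered by allocating an equal number of participants in both intervention and control groups at each participating centre". It then points to fidelity assessment and interviews as further measures.

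**The concern.** Blocking within centre makes the arms alike on whatever differs between centres. That gain reaches the standard error only if the analysis includes centre. A two-sample t-test leaves the between-centre variance in its error term although the design has removed it from the treatment contrast, so the test is conservative and less powerful than it could be.

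The second feature acts the other way. Patients counselled by the same social worker share that person's skill and style in delivering the modules, and controls do not. Their outcomes may be positively correlated in one arm, and a test that treats them as independent then has too small a standard error.

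The Discussion's remedy fits the first feature and not the second. A centre's case mix or usual care affects both arms and cancels in a balanced comparison. How well the local social worker delivers the counselling affects one arm and cannot cancel. A reader of that sentence could believe that the design has reduced a source of error that it leaves untouched.

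**Working it through.** **The plan's own figure.** Sample size gives "Thirty-seven patients will be needed in each condition", "assuming a significance of 5 % (two-tailed) and power of 80" %, and "detecting a clinically relevant change of eight points on the primary outcome variable". No SD is stated, so 37 can only be back-solved:

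- SD = 8 / [(1.960 + 0.842) × √(2/37)] = 12.28 if 37 per arm are analysed.
- SD = 10.3 if 37 already allows for the 30% drop-out (37 × 0.7 ≈ 26 analysed).

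**Assumed inputs.** The article gives no ICC; 0.05 and 0.10 are used for both components. Ten social workers, one per centre, is an inference. It gives m = 37/10 = 3.7 intervention patients each.

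**Size of an unpaired t-test that ignores both features.** Set the total variance to 1, the centre ICC to ρc and the social-worker ICC to ρs. The test works with a variance of about 2/37 for the difference. The true variance is [(1 − ρc + 2.7ρs) + (1 − ρc)]/37, because m − 1 = 2.7. The ratio of true to assumed variance is R = 1 − ρc + 1.35ρs, and the size is 2[1 − Φ(1.96/√R)].

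The formula was checked by simulation: 200,000 trials per row, ten centres with three or four patients per arm, Monte Carlo error about 0.05 points. The last column adds fixed centre effects but no social-worker term.

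| ρc | ρs | R | Size, formula | Size, simulated | Size with centre only, simulated |
|---|---|---|---|---|---|
| 0.05 | 0 | 0.950 | 4.4% | 4.5% | 5.0% |
| 0.10 | 0 | 0.900 | 3.9% | 4.0% | 5.0% |
| 0 | 0.05 | 1.068 | 5.8% | 5.8% | 5.9% |
| 0 | 0.10 | 1.135 | 6.6% | 6.6% | 6.9% |
| 0.05 | 0.05 | 1.018 | 5.2% | 5.3% | 5.9% |
| 0.10 | 0.10 | 1.035 | 5.4% | 5.6% | 7.1% |
| 0.05 | 0.10 | 1.085 | 6.0% | 6.1% | 7.0% |
| 0.10 | 0.05 | 0.968 | 4.6% | 4.8% | 6.0% |

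The two omissions largely offset. Adjusting for centre removes the offset and exposes the social-worker part.

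**Power lost by leaving out centre** (SD 12.28, no social-worker effect). The naive standard error is 12.28 × √(2/37) = 2.855, and 8/2.855 = 2.802.

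- ρc = 0.05: without centre Φ[(2.802 − 1.96)/√0.95] = 80.6%; with centre Φ[2.802/√0.95 − 1.96] = 82.0%. Loss 1.4 points.
- ρc = 0.10: 81.2% against 84.0%. Loss about 2.7 points.

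Allowing for the nine degrees of freedom spent on centre, simulation puts the losses at 1.2 and about 2.6 points.

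**Sensitivity of the design effect, 1 + (m − 1)ρs, at ρs = 0.05.**

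- Ten social workers, m = 3.7: 1.135.
- Five social workers, m = 7.4: 1.32.
- Twenty social workers, m = 1.85: 1.04.
- Ten social workers, 26 analysed per arm, m = 2.6: 1.08.

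**How well the social-worker variance can be estimated.** With ten clusters of about 3.7 and no centre effect, the analysis-of-variance estimate is zero or negative in about 41% of trials at ρs = 0.05 and 30% at 0.10.

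**The case against.** The strongest reply is that a journal article condenses the plan. Data analysis defers to a detailed plan, and centre terms, random effects and degrees of freedom normally belong there. A reader might infer that the trial will certainly be analysed without centre, and the article does not establish that. What stands is narrower: it names one between-group test, that test has no centre term, and the list of what the later plan will add mentions neither strata nor clustering.

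The Discussion says only that equal allocation partly helps, and it adds fidelity checks and interviews. A reader might infer that it claims a full remedy, or says something about standard errors. It does neither. Social workers also recruit patients for both arms and often know them already, so not every social-worker influence is confined to one arm. These points limit the criticism to delivery of the counselling. For that part, allocation does nothing, and descriptive fidelity work does not change a standard error.

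A reader might also conclude that the confidence interval is wrong in both directions. One interval cannot be both too wide and too narrow, and the joint figures show a small net error. With 26 analysed per arm, the joint size is about 4.4% to 5.5%.

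Finally, all figures are for an unpaired test, whereas the article calls its test paired. Patients in the two arms are not matched, so a paired test between arms is a separate error, and mending it would bring in neither centre nor social worker.

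**Conclusion.** The point holds at modest size. The named test does not reflect the blocking by centre. Under assumed centre ICCs of 0.05 to 0.10 it is conservative, with size about 4.4% to 4.0%, and loses between one and three points of power. Social-worker clustering alone would raise type I error to about 5.8% to 6.6% if about ten people deliver the counselling. With both present the unadjusted test sits near 5% to 6% when the two ICCs are equal or the social-worker ICC is the larger, and at about 4.6% to 4.8% in the reverse case.

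This offset depends on two unknown ICCs and is no reason to leave the analysis as it is. It does mean that adding centre alone is incomplete, since that leaves about 6% to 7%. The figures do not support a claim that the planned comparison would be seriously invalid. The ICCs are assumptions, the number of social workers is inferred, and the SD is back-solved. Only the mismatch between blocking and test, and the limit of the Discussion's argument, follow from the text itself.

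**What to change.** In Data analysis, replace the t-test by a between-group model for the primary outcome that includes centre. Prespecify a sensitivity analysis that adds a social-worker random effect in the intervention arm only, with small-sample degrees of freedom such as Satterthwaite's. State in advance that a variance estimated from about ten small clusters is imprecise and will often come out as zero. For that reason the term belongs in a sensitivity analysis and not in the primary model. Controls may take up the intervention after the third measurement, so the one-arm structure fits the comparisons up to that point; the plan should say how the last measurement is handled.

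In the Discussion, say that allocation per centre balances centre, and that variation between social workers in delivering the counselling is examined in the sensitivity analysis.

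The cost is wording and a little modelling. Centre is known from randomisation, and social workers already complete a registration for each participating patient, so it should be enough to make sure that the form identifies who gave the counselling. A fixed centre term uses up to nine degrees of freedom, which the power figures above allow for.

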#### Quantitative measurements

To determine the effects of the intervention on the short- and long-term, repeated quantitative measurements will be conducted (four survey measurements over a period of 13 months). These surveys will be completed by the participants in both the intervention and control groups.

The primary outcome will be fatigue severity, measured by a subscale of the CIS-fatigue [43]. The secondary outcome will be quality of life (kidney disease specific), as measured by the KDQOL [48]. Questionnaires on coping style, illness cognitions/perceptions, catastrophizing thoughts, depression, social support and overall perceptions of mastery and control will be included since these outcomes may be potential moderating or mediating factors. In addition, various medical parameters and demographics will be studied as potential modifiers. All outcome measures and assessment instruments are listed in Table 1.

**Table 1 Tab1:** Measures and instrumentation

	Instrumentation	T0	T1	T2	T3
Primary outcome measures					
Fatigue severity	Checklist Individual Strength (CIS-fatigue) [43]	x	x	x	x
Secondary outcome measures					
Quality of life	Kidney Disease and Quality of Life Short Form (KDQOL-SF) [48]	x	x	x	x
Mediating/moderating variables					
Social support	Social Support Inventory (SSL-I + SSL-D) [58] + subscale Utrechtse Coping Lijst (UCL) [59]	x	x	x	x
Illness cognitions	Illness Cognition Questionnaire (ICQ) [60]	x	x	x	x
Illness perceptions	Illness Perception Questionnaire (IPQ-R) [61]: subscale emotional representation	x	x	x	x
Coping	Cognitive Emotion Regulation Questionnaire (CERQ) [62]	x	x	x	x
Catastrophizing thoughts	Fatigue Catastrophizing Scale (J-FCS) [63, 64]	x	x	x	x
Mastery	Mastery Scale [65]	x	x	x	x
Depression	Patient Health Questionnaire: Depression (PHQ-9) [66]	x	x		
General effect modifiers					
Demographic variables	Self-report: age, gender, education, ethnicity, social status, employment	x			
Medical history and comorbidity	Self-report: treatment, treatment frequency, transplantability	x			
Medical parameters	Medical records: sleep medication, Epo, Hb, Urea, Creatinine, Protein, Albumin, CRP, weight, height	x			x

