For each individual in the intervention group, measurements will be obtained prior to the start of the study period (T0 - baseline), immediately after the intervention period of 16 weeks (T1 - post- treatment), three months after the intervention period (T2 – short-term follow-up) and nine months after the intervention period (T3 – long-term follow-up). For patients participating in the control group, measurements will be obtained according to the same time frame (baseline; + 16 weeks; + three months; + six months). (Participants will be able to decide themselves how and when they fill out the questionnaires (online/paper-pencil; at the dialysis centre/at home). The overall duration of the study will be 13 months for each participant (in both intervention and control group).

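### Controls may take up the intervention after T2, so the T3 comparison no longer measures intervention against usual care to the extent that they accept

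*Protocol article*

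**What the plan says.** Under Randomisation, for ethical reasons and if the patient so wishes, "patients allocated to the control group will be offered the opportunity to participate in the intervention group after the third measurement".

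Under Quantitative measurements, the schedule is "four survey measurements over a period of 13 months", and "These surveys will be completed by the participants in both the intervention and control groups". The purpose is given as "To determine the effects of the intervention on the short- and long-term, repeated quantitative measurements will be conducted". The second follow-up point is "three months after the intervention period (T2 – short-term follow-up") and the last is "nine months after the intervention period (T3 – long-term follow-up"). Controls are kept on the same time frame, and Table 1 has fatigue and quality of life measured at all four points.

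The primary objective at the end of the Background compares the intervention with usual care and names no time point. Sample size describes the primary outcome as having "four repeated measurements". Data analysis compares the arms on primary and secondary outcomes by a t-test. It names no time point and defers a detailed plan.

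No section says how T3 is to be read once controls have had the offer, and the limitations in the Discussion do not mention it.

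**The concern.** The only measurement labelled long-term comes after the usual-care arm has been offered the treatment under test. Any control who accepts is no longer a usual-care patient at T3, and those who accept select themselves. An arm comparison at T3, or an overall repeated-measures effect that includes T3, would then answer a different question from the stated objective.

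The practical risk is one of interpretation. If the intervention has a lasting benefit and controls catch up after crossing over, the arms converge at T3. The report could then say that the effect was lost at long-term follow-up when it was not. Analysis alone cannot repair this. There is no untreated control arm at T3 beyond those who declined, and dropping or censoring the crossovers would bring in selection bias of unknown direction.

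**Working it through.** **1. Which measurement is the third?** Four measurements are listed in order: T0, T1, T2, T3. Counting from baseline, the third is T2, three months after the intervention period.

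**2. Is there time for the intervention to act before T3?** Inputs: a course of 16 weeks (Study intervention), T2 at three months and T3 at nine months after the intervention period, and 13 months overall (Quantitative measurements).

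- 16 weeks = 16 × 7 / 30.44 = 3.7 months, and 3.7 + 9 = 12.7 months. This agrees with the stated 13 months.
- T2 to T3 is 9 − 3 = 6 months, about 26 weeks. A control who starts at once after T2 could finish about 26 − 16 = 10 weeks before T3. This is the earliest case; a later start shortens the interval.
- The Abstract gives the last follow-up as six months. On that reading the gap is 3 months, about 13 weeks. Since 13 < 16, the same control would still be in treatment at T3.

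T3 is open to crossover on either schedule.

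**3. The plan's own figure.** Sample size gives 37 per arm for 8 points, two-sided 5%, 80% power. No SD is stated, so 37 cannot be reproduced directly. Solving for the SD that yields it:

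- Normal approximation: SD = 8 / [(1.960 + 0.842) × √(2/37)] = 8 / 0.651 = 12.28.
- Noncentral t: SD = 12.12.

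This SD is back-solved and takes 37 as the number evaluable.

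**4. Dilution at T3.** Let c be the share of controls who take up the intervention. Assume a lasting 8-point effect that crossovers obtain in full by T3. The expected difference is 8 × (1 − c). The documents give no value for c, so a range is shown, with two-sample t-test power at 37 per arm and SD 12.12:

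| Uptake c | Expected T3 difference | Power |
|---|---|---|
| 0% | 8 points | 80% |
| 25% | 6 points | 56% |
| 50% | 4 points | 29% |
| 75% | 2 points | 11% |

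The article does not say whether 37 already allows for the expected 30% drop-out. If it does, about 26 per arm are evaluable and the back-solved SD is about 10.3 (normal approximation). The power column is then practically the same, because the SD is again chosen to give 80% at c = 0. The relative loss does not depend on settling that question.

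**The case against.** Several points on the other side are sound.

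- **The offer is optional and uptake is unknown.** A reader might infer that T3 is certainly contaminated. The documents do not support that: with no uptake nothing is lost, and the figures above are conditional on assumed uptake. Dilution towards no effect also presumes that the intervention works and that crossovers gain from it.
- **The main question survives.** A reader might infer that the trial's primary result is compromised. It is not. T1 and T2 precede the offer, nothing in the article makes T3 the primary time point, and the stated objectives set no long-term aim. That aim appears only under Quantitative measurements.
- **The analysis plan may choose the time points.** Data analysis is brief and defers the detail. The mention of four measurements under Sample size includes baseline, so it does not prove that T3 enters the primary contrast. This limits the point but does not remove it. The offer and the T3 label are both fixed in this article, and no later plan can restore a usual-care arm.
- **T3 as randomised is still a valid comparison.** This stands, but it is valid for immediate against optional delayed counselling, not for intervention against usual care.
- **The third measurement might have been meant as T3.** If so, the problem disappears. The count of four measurements makes T2 the natural reading, and the text should settle it.

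**Conclusion.** The point holds in conditional form. The offer to controls and the use of T3 as long-term follow-up for intervention effects do not fit together as written. To the extent that controls accept, the T3 contrast departs from the stated comparison with usual care. If the intervention works, that contrast shrinks in proportion to uptake: half the controls crossing over with full benefit would turn 8 points into 4. The size rests on three assumptions that the documents do not supply: the uptake, a full and lasting effect in crossovers, and the back-solved SD. The mismatch itself rests on none of them. T1 and T2 stand as planned.

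**What to change.** 1. Under Randomisation, name the time point of the offer by its label (T2, if that is meant).
2. Under Data analysis, state that the between-arm comparison with usual care on primary and secondary outcomes uses T1 and T2 only, and that no overall repeated-measures effect against usual care includes T3.
3. Record the start date and the number of sessions for each control who takes up the offer. The registration forms described under Implementation fidelity already cover number and duration of sessions, so this is a small extension.
4. Report T3 as randomised, labelled as immediate versus optional delayed intervention, with the uptake beside it. Treat maintenance within the intervention arm as descriptive only: patients enter on a CIS-fatigue score of at least 35, so regression to the mean is likely, and 30% drop-out is expected.
5. Amend the long-term aim under Quantitative measurements so that no randomised long-term effect against usual care is claimed.

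The cost is wording and a little record-keeping. No further patients are needed, and the offer to controls is unchanged. The real price is a smaller claim: the trial gives no randomised long-term estimate against usual care.
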